### Storage

The IMP should be stored at room temperature (25^o^C**/**77^o^F ) in its original container.  On site, all IMP should be stored in a secure location, in a temperature controlled environment, preferably with a temperature log maintained daily, and may be dispensed only by the investigator or by a member of staff specifically authorised by the investigator, or by the pharmacist, as appropriate.  Any deviations from the recommended storage conditions should immediately be reported to the sponsor and the use of the IMP interrupted until the Sponsor has given authorisation for its use.

### Dispensing of Study Drug

The dispensing of the IMP will be carefully recorded on the appropriate drug accountability forms provided by the sponsor, and accurate accounting will be available for verification by the sponsor, and the sponsors monitor at each visit. Information recorded will include:

Dates, quantities, batch numbers, kit numbers for IMP, expiry dates and trial numbers assigned to the subjects.

### Return or Destruction of Study Drug

Any unused IMP must not be discarded or used for any purpose other than the present trial. Subjects should be instructed to return any unused IMP and all empty blisters and packaging.

**In summary the IMP accountability records will include:**

Confirmation of the IMP delivery to the trial site

The inventory at the site of IMP provided by the Sponsor

The use of each dose by each subject

Any returns or unused product

Dates, quantities, batch numbers, kit numbers for IMP, expiry dates and trial numbers assigned to the subjects.

# Laboratory Assays

**Routine blood tests** (to be undertaken after an 8 hour fast):

If a test result from the haematology, biochemistry, or urinalysis falls outside the normal range, the clinical significance of such a result will be evaluated and the need for repeat testing considered by an Investigator.

The following tests will be taken at each clinic visit as specified in the protocol (section 7)

FBC (full blood count), U+E’s (serum electrolytes, urea and creatinine), Ca (calcium), PO_4_ (phosphate), bilirubin, ALT (alanine transaminase), ALP (alkaline phosphatase), CRP (C reactive protein), lipid profile, albumin, glucose, serum magnesium, 25 (OH) vitamin D (vitamin D levels) and PTH

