**Statistical Methodology and Analysis**

All data will be analysed by the principal investigator with the support of a trained statistician and the chief investigator. The data will be assessed for normality and the relevant parametric or non−parametric tests applied. The statistical programmes SPSS and STATA will be used.

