## Blinding of Study Drug

Both the investigators and patients will be blinded to the study drug. Mawdsley Brooks UK will facilitate randomisation and blinding of the study subjects. A master randomisation list will be held at Mawdsley Brooks UK with a copy kept at the Royal London Hospital Pharmacy department.

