# Study Procedures and Schedule of Assessments

Patients will be examined and assessed by an investigator at the renal outpatient department of the Royal London Hospital. Cardiac MRI will take place at the London Chest Hospital (aprox 20 min walk from RLH)

All assessments will be similar between the two groups. At each study point, participants will undergo the relevant assessment and will also receive one dose of the study drug to ensure compliance.

The table below details each study time point and exactly what will occur. Each Action is explained in more detail below.

| **Visit** | **Drug** | **Action** | **Action** | **Action** | **Action** | **Action** | **Action** | **Action** | **Action** | **Action** |
| --- | --- | --- | --- | --- | --- | --- | --- | --- | --- | --- |
| 0 weeks | Washout |  |  |  |  |  |  |  | Bloods | Examination |
| 2 weeks | n |  | Microcirc |  |  |  |  |  |  | Examination |
| 1 month (4 weeks) | y | ECG | Microcirc | SF 36 | Urine | MRI/echo | 24hr BP | USS neck | Bloods | Examination |
| 2 month | y |  | Microcirc |  | Urine |  |  |  | Bloods | Examination |
| 3 months | y |  |  |  |  |  |  |  | Bloods | Examination |
| 4 months | y |  | Microcirc |  | Urine |  |  |  | Bloods | Examination |
| 5 months | y |  |  |  |  |  |  |  | Bloods | Examination |
| 6 months | y |  |  |  |  |  |  |  | Bloods | Examination |
| 7 months | n | ECG | Microcirc | SF 36 | Urine | MRI/echo | 24hr BP | USS neck | Bloods | Examination |

**Time** – 0 weeks refers to recruitment, consent and enrolment. Randomisation will occur at month 1 (4 weeks after recruitment). The study will end at month 7 after recruitment. Patients will receive the study drug for 6 months in total.

**Drug** – at month 1 (week 4) patients will be randomized to and receive at that visit either placebo or ergocalciferol. Patients will receive all 9 capsules of study medication at this time. They will be required to take 1 dose weekly at home in the first month. Further study medication will be taken at subsequent clinic visits and patients will be observed swallowing their medication either by pharmacy staff or an investigator.

**ECG** – a 12 lead cardiac ECG will be undertaken. This is a painless, non-invasive procedure.

Duration 5 minutes.

**Microcirc** – This process involves four assessments of the microcirculation and will take place at a clinic visit in the same room.

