Duration – 1 hour

**Echo –** cardiac ultrasound conducted at the Royal London Hospital

Duration – 15 minutes

**24 hour blood pressure –** Patients will be fitted with a blood pressure cuff and portable recording device which will measure ambulatory blood pressure over a 24 period.

Duration - 24 hours

**Ultrasound neck –** to be undertaken by trained ultrasonographers and an investigator who will be fully trained in this technique. It will involve a gentle, non-invasive scan of the large blood vessels in the neck.

Duration – 10 minutes

**Bloods** – Will be taken by an investigator or trained clinic staff. Only one venepuncture will be required to minimize discomfort.

Duration - 5 minutes

**Examination** – Patients will undergo a routine clinical examination by an investigator including blood pressure measurement

Duration - 10 minutes.

**Recording of study data** – At each visit, clinical entries will be recorded in patient’s record. Data derived from the above investigation will be documented on the case report form. These files will be kept in a locked cabinet in a locked room in the Renal Out Patient department, Royal London Hospital. This department has a lock which requires access via staff ID cards.

**Assessments for efficacy** –

In the ergocalciferol treated group:

Vitamin D levels

We expect these will increase in patients treated with ergocalciferol

Microcirculatory assessments:

We expect pulse wave velocity to reduce, iontophoresis to show improved microcirculatory function by laser colour Doppler, skin AGE deposition to decrease and sub lingual microcirculation to improve.

Imaging

We expect reduction in LV mass and improvement in ejection fraction

Clinical

We expect reduction in BP, progression of renal dysfunction and reduction in proteinuria

**Assessment for safety –** the most likely side effect of ergocalciferol is hypercalcaemia. We will measure calcium levels at each clinic visit and screen patients for the symptoms of hypercalcaemia. If symptomatic hypercalcaemia is present, the patient will be withdrawn from the study as per section 4.4.1. If the serum calcium is elevated in the absence of associated symptoms, as per standard clinical medical care, the study drug will be omitted at that visit. The patient will then attend the next visit as per the protocol and if the calcium level at that visit is below 2.6 mmol/L, the study drug will be administered and the patient will follow the protocol from that point onwards.

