## Unblinding Procedures

Patients and investigators will be unblinded if they are admitted to hospital with hypercalcaemia. Unblinding will be required as there are a number of common medical conditions (myeloma, tuberculosis, sarcoidosis etc) that can cause hypercalcaemia and should be ruled out urgently if a study patient who is taking placebo rather than ergocalciferol presents with symptoms/signs of hypercalcaemia.

Mawdsley Brooks UK will hold a master randomisation list which will be able to identify which arm any subject is in. There is a 24 hour trial hotline which can be contacted by clinical staff at any time should unblinding be required for medical reasons. Furthermore, individual code break envelopes will be available to clinicians at the Royal London Hospital. All renal staff will have access to code break procedures and envelopes which will be locked in a secure office with an entry code on the door.

Code-breaks should only occur when absolutely necessary and beneficial to the patient. In the event of a code break, the sponsor and PI will be informed.

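### 25(OH)D is measured at every post-dose visit with no provision to withhold it from the investigators, so investigator blinding can be compromised from the month-2 result onward

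*Combined protocol and SAP*

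**What the plan says.** The section Blinding of Study Drug states: "Both the investigators and patients will be blinded to the study drug". The means described are matching capsules and a master randomisation list held by the supplier, with a copy in the hospital pharmacy.

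Laboratory Assays defines a routine panel: "The following tests will be taken at each clinic visit as specified in the protocol (section 7". The list ends with "serum magnesium, 25 (OH) vitamin D (vitamin D levels) and PTH". The same section has an investigator evaluate any haematology, biochemistry or urinalysis result outside the normal range.

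In the schedule of assessments, the only visit without bloods is the two-week visit, which precedes randomisation. Bloods are taken at months 2, 3, 4, 5, 6 and 7, all after dosing starts at month 1. In the Appendix 1 arm they are taken at months 2, 3 and 4. 1,25(OH)D is measured at visit 3 and at the last visit.

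On 25(OH)D as an efficacy measure, Study Procedures says: "We expect these will increase in patients treated with ergocalciferol". Dose Rationale (section 1.5) also hopes for lower PTH. Neither section gives a size, an SD or a time course.

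On analysis, the Study Summary says: "All data will be analysed by the principal investigator with the support of a trained statistician and the chief investigator".

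**The concern.** Matching capsules protect the blind only while nothing else reveals the arm. A serum level of the drug's own metabolite, read repeatedly in patients selected for a low level, can reveal it.

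The people who could see the result also influence the outcome at several points:
- An investigator examines and assesses the patients. Some primary measures need operator judgement: tape-measured cuff distances for pulse wave velocity, and sublingual video read later with no blinded reader specified.
- The principal investigator judges withdrawal for non-compliance, for adverse reaction and for newly started drugs.
- Investigators may add blood pressure therapy, and 24-hour blood pressure is a secondary endpoint.
- The principal investigator leads the analysis, and the Study Summary leaves the choice between parametric and non-parametric tests until the data have been examined.

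An investigator who has a good idea of the arm could shift any of these without intending to. The analysis could not reliably remove that bias afterwards.

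**Working it through.** **Is there any figure to reproduce?** No. The plan does not quantify how well 25(OH)D separates the arms. Its one design calculation (32 per arm) does not use 25(OH)D and would not change if the results were masked.

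**Do the results reach the investigators?** The plan does not say who receives the 25(OH)D and PTH reports. Four provisions point the same way:
1. An investigator evaluates out-of-range biochemistry (Laboratory Assays).
2. Calcium from the same visits is acted on at each visit (Study Procedures, assessment for safety).
3. Data from the listed investigations, which include bloods, go on the case report form (Study Procedures).
4. The principal investigator keeps the case report forms, and fields may be blank only if data are unavailable or not applicable (Case Report Forms).

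No section masks the results, names an unblinded reviewer, or requires a blinded assessor or analyst. Access is a strong inference, not a stated fact.

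**When could it matter?** The first dose is at month 1, so the first post-dose blood is at month 2.

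| Visit | Microcirculatory assessment | Post-dose bloods drawn at earlier visits |
|---|---|---|
| Month 2 | yes, without sublingual imaging | none (first sample is drawn at this visit) |
| Month 4 | yes, with sublingual imaging | months 2 and 3 |
| Month 7 | yes, with sublingual imaging | months 2 to 6 |

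In the Appendix 1 arm only the month-4 assessment follows earlier post-dose bloods.

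**How revealing is one before/after pair?** All inputs here are assumptions: a mean rise d on active drug, no change on placebo, and a within-person SD s for a single value. The SD of a change is s√2. With the cut at d/2, the chance of naming the arm correctly is Φ(d / (2s√2)); guessing gives 50%.

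| d (nmol/L) | s = 12 | s = 8 |
|---|---|---|
| 15 | Φ(0.442) = 67% | Φ(0.663) = 75% |
| 25 | Φ(0.737) = 77% | Φ(1.105) = 87% |
| 40 | Φ(1.179) = 88% | Φ(1.768) = 96% |

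**If response varies between patients.** Suppose the rise has an SD of 15 nmol/L across active patients (also assumed). Their change then has SD √(2s² + 225), and the overall figure is the mean of the two arms. At d = 25:
- s = 12: (Φ(12.5/22.65) + Φ(12.5/16.97))/2 = (0.709 + 0.769)/2 = 74%
- s = 8: (Φ(12.5/18.79) + Φ(12.5/11.31))/2 = (0.747 + 0.865)/2 = 81%

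**Wider grid.** Taking the SD of change directly as 10 to 25 nmol/L, Φ(d / (2 × SD)) gives 69% to 58% for a rise of 10, 84% to 66% for 20, 93% to 73% for 30, and 98% to 79% for 40.

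**PTH.** Ethical Considerations gives a median of 11.7 and an SD of 19.44 pmol/L in a similar local group. With that spread between patients, a single value says little about the arm. A change from a patient's own baseline might say more, but the plan gives no figure for it.

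**The case against.** A reader might infer that the double blind is simply lost within a month or two of dosing. The documents do not support that. The size and SD of the rise are unstated, and at the low end of the ranges the guess is only modestly better than chance. The model also flatters the separation: it assumes no change on placebo, although patients are selected for a low value and may drift upward, and dosing falls from weekly to monthly after the first month. Nothing suggests that patients are told their levels, so their own blinding is not shown to be at risk. Allocation is not affected either.

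It can also be said that result routing is unstated and that the laboratory instructions listed among the attachments are not reproduced. That is fair. It limits the claim to the absence of any masking provision in the plan, which stands.

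Several measures do limit operator influence. Iontophoresis, on which the trial is powered, uses fixed currents and a laser Doppler monitor. Skin autofluorescence is a repeated device reading, and the analysis has a statistician's support. No withdrawal criterion names 25(OH)D or PTH, so that route runs only through discretion. These points reduce the likely bias but do not remove it.

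A reader might also see a second leak in Unblinding Procedures, which says: "All renal staff will have access to code break procedures and envelopes". The same sentence places the envelopes in a locked office with an entry code. The section then limits code-breaks to necessity and has the sponsor and principal investigator informed. It is not evidence that the blind is open, and no change is asked for there.

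**Conclusion.** The point holds as a material, uncontrolled risk to investigator blinding from the month-2 result onward. The absence of any masking provision can be read from the plan with high confidence. That investigators would see the results is a strong inference.

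The size rests wholly on assumed values: about 67% to 96% correct identification from one pair for rises of 15 to 40 nmol/L and a within-person SD of 8 to 12. It is lower if response varies between patients (74% to 81% instead of 77% to 87% at a rise of 25). 25(OH)D carries the argument; PTH adds little on the figures available.

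The month-2 microcirculatory assessment is largely spared because the first post-dose blood is drawn at that same visit. Exposure falls mainly on months 4 and 7, or on month 4 alone in the Appendix 1 arm, and on discretionary withdrawals, added blood pressure therapy and the analysis. The direction and size of any resulting bias cannot be estimated from the documents.

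**What to change.** 1. From the first post-dose sample until database lock, report 25(OH)D, 1,25(OH)D and PTH only to a restricted file held outside the assessing and analysing team. Pharmacy is a natural holder because it already has a copy of the randomisation list. Screening and baseline values stay visible, since eligibility depends on them.
2. Take these three assays out of the investigator's review of out-of-range results, and mark their post-dose case report form fields as held elsewhere so that the rule on blank fields is not breached.
3. Keep calcium and the rest of the safety panel visible. The stated rules on withdrawal and on omitting a dose use calcium and symptoms, so they are unchanged.
4. Code the stored sublingual videos so that they are read without patient, visit or laboratory information.
5. Apply the same wording to the Appendix 1 arm.

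The cost is a restricted-results flag at the hospital laboratory, a numbering step for the videos and a short protocol amendment. The sample size and visit schedule do not change. The one downside is that the holder must pass on any value that needs clinical action. The clinicians should agree beforehand how that is decided, and each release should be logged.

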**Other blood tests**

These tests will be taken at visits 3 and 9

1,25 OH vitamin D, Trop T (troponin T), renin, aldosterone

**Routine samples (urine ~ 25 mls):** urine sodium, urine PCR (protein:creatinine ratio)

A range of in vitro assessments to establish measures of oxidative stress and platelet activity will be conducted in a laboratory at the Royal London Hospital with an established protocol for these techniques.

# Study Procedures and Schedule of Assessments

Patients will be examined and assessed by an investigator at the renal outpatient department of the Royal London Hospital. Cardiac MRI will take place at the London Chest Hospital (aprox 20 min walk from RLH)

All assessments will be similar between the two groups. At each study point, participants will undergo the relevant assessment and will also receive one dose of the study drug to ensure compliance.

The table below details each study time point and exactly what will occur. Each Action is explained in more detail below.

| **Visit** | **Drug** | **Action** | **Action** | **Action** | **Action** | **Action** | **Action** | **Action** | **Action** | **Action** |
| --- | --- | --- | --- | --- | --- | --- | --- | --- | --- | --- |
| 0 weeks | Washout |  |  |  |  |  |  |  | Bloods | Examination |
| 2 weeks | n |  | Microcirc |  |  |  |  |  |  | Examination |
| 1 month (4 weeks) | y | ECG | Microcirc | SF 36 | Urine | MRI/echo | 24hr BP | USS neck | Bloods | Examination |
| 2 month | y |  | Microcirc |  | Urine |  |  |  | Bloods | Examination |
| 3 months | y |  |  |  |  |  |  |  | Bloods | Examination |
| 4 months | y |  | Microcirc |  | Urine |  |  |  | Bloods | Examination |
| 5 months | y |  |  |  |  |  |  |  | Bloods | Examination |
| 6 months | y |  |  |  |  |  |  |  | Bloods | Examination |
| 7 months | n | ECG | Microcirc | SF 36 | Urine | MRI/echo | 24hr BP | USS neck | Bloods | Examination |

**Time** – 0 weeks refers to recruitment, consent and enrolment. Randomisation will occur at month 1 (4 weeks after recruitment). The study will end at month 7 after recruitment. Patients will receive the study drug for 6 months in total.

**Drug** – at month 1 (week 4) patients will be randomized to and receive at that visit either placebo or ergocalciferol. Patients will receive all 9 capsules of study medication at this time. They will be required to take 1 dose weekly at home in the first month. Further study medication will be taken at subsequent clinic visits and patients will be observed swallowing their medication either by pharmacy staff or an investigator.

**ECG** – a 12 lead cardiac ECG will be undertaken. This is a painless, non-invasive procedure.

Duration 5 minutes.

**Microcirc** – This process involves four assessments of the microcirculation and will take place at a clinic visit in the same room.

1. Pulse wave velocity. An assessment of the speed of the pulse transmission in the major blood vessels of the body. Patients will have blood pressure cuffs placed around the thigh and neck. The cuff around the neck poses NO DANGER TO THE PATIENT AS IT ONLY INFLATES TO 60mm Hg – BELOW SYSTOLIC BLOOD PRESSURE. At worst, patients may feel a gentle pressure sensation around the neck. FULL RESUCITATION EQUIPMENT IS AVAILABLE ON SITE AND THE INVESTIGATORS AND CLINIC STAFF ARE TRAINED IN ADVANCED LIFE SUPPORT TECHNIQUES

Duration – 5 minutes

2. Iontophoresis. An assessment of skin microvascular function. Two compounds (AcH and SNip) are transmitted through the skin by the use of a very low electrical current into the small blood vessels located just under the skin. A laser Doppler probe records the response of the microvasculature. This is a non-invasive test and the drug dose is too low to cause any systemic absorption. Minor skin irritation has been reported but is usually mild and self limiting.

Duration - 15 minutes

3. Skin autofluorescence – An assessment of the build up of advanced glycation end products (AGE), which are a marker of oxidative stress. Patients place their arm over an ultraviolet light and results of AGE product accumulation are downloaded to a computer. This is a painless and non-invasive test.

Duration – 5 minutes.

Sublingual microvascular flow using sidestream darkfield (SDF) imaging – this is a non-invasive imaging tool to assess intra-vital capillary blood flow. A small camera (0.7cm) with a replaceable sterile cap is placed under the tongue in a similar way to temperature measurement with a mercury thermometer. 3 separate images are collected during one reading. These recordings will occur at visit 3, 6 and 9.

Duration – 5 minutes

**SF 36 –** Patients will be asked to fill in this standardized questionnaire about quality of life.

Duration - 10 minutes.

**Urine –** patients will be asked to give a clean catch urine specimen when they arrive at clinic which will be divided into 3 samples (urine sodium, urine calcium and urine PCR). Urine samples will be spun down so no cellular component will be retained or studied.

Duration – 5 minutes

**MRI –** Cardiac MRI scanning will take place at the London Chest Hospital and will be supervised by specialist medical and radiography staff. We will measure left ventricular mass and ejection fraction. The examination will not usually require contrast media to be injected.

Duration – 1 hour

**Echo –** cardiac ultrasound conducted at the Royal London Hospital

Duration – 15 minutes

**24 hour blood pressure –** Patients will be fitted with a blood pressure cuff and portable recording device which will measure ambulatory blood pressure over a 24 period.

Duration - 24 hours

**Ultrasound neck –** to be undertaken by trained ultrasonographers and an investigator who will be fully trained in this technique. It will involve a gentle, non-invasive scan of the large blood vessels in the neck.

Duration – 10 minutes

**Bloods** – Will be taken by an investigator or trained clinic staff. Only one venepuncture will be required to minimize discomfort.

Duration - 5 minutes

**Examination** – Patients will undergo a routine clinical examination by an investigator including blood pressure measurement

Duration - 10 minutes.

**Recording of study data** – At each visit, clinical entries will be recorded in patient’s record. Data derived from the above investigation will be documented on the case report form. These files will be kept in a locked cabinet in a locked room in the Renal Out Patient department, Royal London Hospital. This department has a lock which requires access via staff ID cards.

**Assessments for efficacy** –

In the ergocalciferol treated group:

Vitamin D levels

We expect these will increase in patients treated with ergocalciferol

Microcirculatory assessments:

We expect pulse wave velocity to reduce, iontophoresis to show improved microcirculatory function by laser colour Doppler, skin AGE deposition to decrease and sub lingual microcirculation to improve.

Imaging

We expect reduction in LV mass and improvement in ejection fraction

Clinical

We expect reduction in BP, progression of renal dysfunction and reduction in proteinuria

**Assessment for safety –** the most likely side effect of ergocalciferol is hypercalcaemia. We will measure calcium levels at each clinic visit and screen patients for the symptoms of hypercalcaemia. If symptomatic hypercalcaemia is present, the patient will be withdrawn from the study as per section 4.4.1. If the serum calcium is elevated in the absence of associated symptoms, as per standard clinical medical care, the study drug will be omitted at that visit. The patient will then attend the next visit as per the protocol and if the calcium level at that visit is below 2.6 mmol/L, the study drug will be administered and the patient will follow the protocol from that point onwards.

